## Abstract

**Background::**

Diabetic peripheral neuropathy (DPN) is one of the most common complications of diabetes mellitus. The main clinical manifestations of DPN include pain, numbness, paraesthesia, and weakness of the lower limbs which often leads to diabetic foot ulceration, eventually resulting in amputation. Based on Traditional Chinese Medicine theory, moxibustion has a great effect on treating and preventing DPN. However, randomized clinical trials done to evaluate the efficacy of this treatment are still lacking. Hence, this study is carried out to evaluate the effectiveness and safety of moxibustion therapy on diabetic peripheral neuropathy.

**Methods::**

This study will be a pilot, interventional, randomized, 2-armed, parallel, singled-masked, controlled trial. A total of 40 diabetes mellitus patients with peripheral neuropathy will be recruited and assigned randomly into 2 groups (moxibustion group and waiting group) at a 1:1 ratio. This trial consists of an 8-week intervention period and a 4-week follow-up period. During the intervention period, the moxibustion group will take 3 moxibustion sessions per week, whereas no intervention will be done on the waiting group to act as the control group. The outcome will be assessed by an outcome assessor who is unaware of the group assignment. The primary outcome will be pain assessment measured with algometry, Leeds Assessment of Neuropathic Symptoms and Signs pain scale, visual analogue scale, and neuropathy pain scale. The secondary outcome will be an evaluation of functional performance capacity with 6 minutes walking test, evaluation of the Foot and Ankle Ability Measure, and serum HbA1c and albumin levels.

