### Study procedure

2.7

At visit 1, the study clinical researcher will check the participants’ vital signs, medical history, physical examination, algometry pain assessment, the Leeds assessment of neuropathic symptoms and signs (LANSS) pain scale, VAS, the Neuropathy Pain Scale (NPS), functional performance capacity with 6 minutes walking test, the foot and ankle ability measure (FAAM), and laboratory tests (includes, serum HbA1c, and serum albumin levels). The intervention group will received moxibustion management for 30 minutes. In the meantime, the clinical researcher will check the participants’ adverse effects.

From visit 2 to 24 (8 weeks), the intervention group will be treated the same manner as visit 1, and clinical researcher will be check the participants’ algometry pain assessment, the LANSS pain scale, VAS, the NPS, functional performance capacity with 6 minutes walking test, the FAAM, and laboratory tests (includes, serum HbA1c, and serum albumin levels) on visit 12 and visit 24.

At visit 25 (follow-up), the clinical researcher will check the participants’ adverse effects and measured the same manner as visit 12 and visit 24.

If any additional visits may be performed at any time by the clinical researcher's judgment, or following the participant's request. In the event of an unexpected visit, the following tests and assessment will be performed: vital signs, checking adverse events, and laboratory tests. The detailed study period is shown in Table 1.

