#### Primary outcome measure

2.9.1

Pain assessment measured with Algometry: It is used to determine sensitivity to pain produced by pressure.

Pain assessment measured with the LANSS: The LANSS Pain Scale is based on analysis of sensory description and bedside examination of sensory dysfunction, and provides immediate information in clinical settings.^[12]^ The possible scores range from 0 to 24, with a score of ≥12 considered to be suggestive of neuropathic pain.

Pain assessment measured with the VAS: A VAS is a measurement instrument that tries to measure a characteristic or attitude that is believed to range across a continuum of values and cannot easily be directly measured. It is often used in epidemiologic and clinical research to measure the intensity or frequency of various symptoms.

Pain assessment measured with the NPS: Scores are based on patient responses to questions about pain intensity. 0 indicates no pain; 10 indicates the most pain imaginable. The NPS is only for use in patients who have already been diagnosed with neuropathic pain.^[13]^

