## Data analysis

3

SPSS will be used in statistical analysis. Continuous variable will be shown as mean ± SD, while categorical variables will be shown as percentages and numbers. The significance will be calculated using Student *t* test for matching data or Wilcoxon-test depending on whether normality can be assumed or not. *P* values <.05 will be considered as significantly different.

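### Four unranked primary pain instruments, no named primary visit and a flat P<.05 raise the primary false-positive risk to as much as 18.5% at one visit, with no rule for mixed results

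*Protocol article*

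**What the plan says.** All references are to the protocol article.

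- **Primary outcome.** The abstract states that the "primary outcome will be pain assessment measured with algometry, Leeds Assessment of Neuropathic Symptoms and Signs pain scale, visual analogue scale" and the neuropathy pain scale. Section 2.9.1 (Primary outcome measure) describes the same four one after another as equals. It gives no order, composite, time point or summary measure.
- **Timing.** Section 2.7 (Study procedure) records all four at visit 1 and again at visits 12 and 24. At follow-up visit 25 they are "measured the same manner as visit 12 and visit 24". No visit is called primary.
- **Threshold.** Section 3 (Data analysis) has one rule for everything: P "values <.05 will be considered as significantly different". The test is a t "test for matching data or Wilcoxon-test depending on whether normality can be assumed or not".
- **Size and purpose.** The abstract says: "A total of 40 diabetes mellitus patients with peripheral neuropathy will be recruited", allocated 1:1, so 20 per arm. The trial is labelled a pilot. Its objective in section 2.1 is nevertheless clinical efficacy and safety, and the Conclusion says the data will show whether moxibustion is effective for diabetic peripheral neuropathy.

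**The concern.** A primary outcome should define one question with one answer. Here four instruments share that status, and the article does not say whether success needs one, some or all of them. If any one may count, the error rate of the headline claim is not 5%. If all four must be positive, there is no inflation but power drops; the article does not choose this rule either.

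The unnamed visit adds a second freedom. Mid-treatment, end of treatment or follow-up could each be presented as the primary result, and the choice could be made after the data are seen.

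At stake is the reading of the trial's main result. If VAS improves and algometry does not, the article gives no basis for calling the trial positive or negative.

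**Working it through.** **Figure in the plan.** The article states only N = 40. It gives no power, effect size, SD or family-wise error rate, so there is no figure to reproduce.

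**Inputs from the article.** Four primary instruments (abstract, section 2.9.1); three post-baseline visits (section 2.7); threshold 0.05 per test (section 3); 20 per arm (40 at 1:1).

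**Assumptions.** Two-sided tests (sidedness is not stated), normal test statistics, between-arm comparisons, and correlations as shown.

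**Step 1: independent tests.** Family-wise error = 1 − (1 − 0.05)^k.
- Four instruments, one visit: 1 − 0.95^4 = 0.185.
- Four instruments × three visits = 12 tests: 1 − 0.95^12 = 0.460.

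For two-sided tests on jointly normal statistics, independence is the worst case (Šidák's inequality), so these are upper limits.

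**Step 2: correlated tests.** The article gives no correlations, so a range is shown. The 12-test column is simulated with the between-instrument and between-visit correlations both set to the value in the row.

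| Correlation | 4 tests, one visit | 12 tests |
|---|---|---|
| 0 | 18.5% | 46.0% |
| 0.3 | 17.4% | 42.1% |
| 0.5 | 15.6% | 35.6% |
| 0.7 | 13.0% | 26.5% |
| 0.8 | 11.4% | 21.1% |

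If one common correlation of 0.8 is instead placed on every pair of the 12 tests, the last figure is 18.6%. The four-test reading is thus about 2.3 to 3.7 times nominal (11.4/5 and 18.5/5).

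**Step 3: how often results would be mixed.** Assume a true effect of 0.8 SD on all four instruments at one visit. Some but not all then reach P<.05 in 73% of simulated trials at correlation 0, 51% at 0.5 and 39% at 0.7. A mixed result is therefore a common outcome even when the treatment works on every scale.

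**Step 4: what a repair costs.** Normal approximation: power = Φ(d/√(2/n) − z), with z the two-sided critical value, d = 0.8 (assumed) and n = 20, so d/√(2/n) = 0.8/√0.1 = 2.530.
- One primary test at 0.05: Φ(2.530 − 1.960) = 72%.
- Holm's first step for four tests, 0.05/4 = 0.0125: Φ(2.530 − 2.498) = 51%.

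The effect detectable with 80% power is (z + 0.842) × √0.1: 0.89 SD at 0.05 and 1.06 SD at 0.0125.

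**The case against.** **Details may sit elsewhere.** This is a condensed article. A multiplicity procedure or analysis visit may be set out in an analysis plan, and Table 1 and the supplementary content cannot be seen here. That stands for the visit: if one is named there, the 12-test reading falls away. It does not rescue the primary outcome. The article itself fixes four unranked primaries and a flat threshold, and a later document choosing one of them would change the published primary outcome.

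**It is a pilot.** The label would carry weight if the aims were feasibility or estimation. The article lists no feasibility endpoint, plans significance tests and promises an answer on effectiveness.

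**Stronger readings that the article does not support.**
- *A false-positive primary result is likely.* Every figure above is below 50%; the risk is inflated, not probable.
- *The plan tests 12 primary comparisons.* Section 2.7 schedules measurements and section 3 does not mention visits. Twelve tests is what the wording permits, not what it says.
- *With 20 per arm, chance findings will dominate.* A valid test at 0.05 has the same false-positive rate at any sample size. A small trial loses power; whether chance dominates depends on effect sizes and priors that the article does not give.
- *LANSS is presented as a classification tool.* Section 2.9.1 gives a 0 to 24 score and a cut-off suggestive of neuropathic pain; it does not call it that. The point does not need this argument.

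**The test named is for matched data.** Read literally, it compares visits within an arm. That is a separate problem. The family-wise figures would then apply to the moxibustion arm's own tests; the between-arm power figures would not.

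**Conclusion.** The point holds. Four unranked primary instruments, no named primary visit, an unadjusted P<.05 and no success rule leave the headline result without a defined criterion, although the article presents the trial as deciding effectiveness.

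The size that rests most directly on the text is up to 18.5% for four instruments at one visit, or about 11% to 17% with assumed correlations of 0.8 to 0.3. The 46% figure is the ceiling if all three visits are also tested and any positive is counted. Both take success to mean at least one positive instrument, which the article neither states nor excludes. The correlations, two-sided testing, between-arm comparison and 0.8 SD effect are assumptions.

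**What to change.** By dated amendment to the protocol and registry entry, made before outcome data are examined by arm, name one primary instrument and one visit. An example is the between-arm difference in VAS at visit 24, which is the end of treatment (3 sessions × 8 weeks = 24). Report the other instruments and visits as secondary, with estimates and 95% confidence intervals. This restores a 5% error rate for the primary claim.

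If all four must stay primary, apply Holm across the four at that one visit and state what counts as success.

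**Cost.** No added patients or measurements. Under the first option three scales lose primary status. Under Holm, power for a given instrument falls from about 72% at 0.05 to about 51% at the first-step level of 0.0125 (assumed 0.8 SD effect, 20 per arm). Later Holm steps are less strict, so 51% is the floor. Recruitment was planned from November 2021 and was incomplete at submission, so enrolment may have begun; the amendment should record its date, its reason and that outcomes had not been examined by arm.

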**Discussion::**

We hope that this trial will provide valuable insights on the efficacy of moxibustion in the management of diabetic peripheral neuropathy.

**Trial registration::**

ClinicalTrials.gov Registry No.: NCT04894461 (URL: https://clinicaltrials.gov/ct2/show/NCT04894461?term=NCT04894461&draw=2&rank=1) Registered on May 20, 2021.

## Introduction

1

Diabetic peripheral neuropathy (DPN) is one of the most common complication of diabetes mellitus patients, with prevalence of 50.7% in Malaysia.^[1]^ It is a crucial factor that can lead to the development of diabetic foot ulceration and is one of the major reasons of nontraumatic lower extremity amputations in many of the high-income nations.^[2]^ The main clinical manifestations of DPN includes pain, numbness, paresthesia, and weakness of the lower limbs, and patients can easily injure their foot unaware, which leads to ulceration, eventually resulting in amputation.^[3]^ Considering how serious the complications can get, DPN should be diagnosed as soon as possible and treat accordingly. However, the efficacy of the treatment is not promising.^[4]^

Many physicians have initiated study to explore how Traditional Chinese Medicine (TCM) can help in DPN therapy. Based on TCM theory, moxibustion can regulate qi and blood, warm meridian, and improve blood circulation, which may help treat and prevent DPN.^[4]^ TCM external treatment are commonly utilized in clinical practice. For instance, acupuncture has been proven to be therapeutically beneficial and is frequently used to treat DPN.^[5,6]^ Moxibustion, on the other hand, was showed in some studies to be able to raise serum superoxide dismutase level,^[7]^ lower free-radical production, protect nerve tissues from damage due to free-radical build-up, and relieve neuro-inflammation, potentially through inhibition of NF-κB and activation of Nrf2.^[8]^ Liu et al^[9]^ found out that moxibustion with methylcobalamin is more effective than using methylcobalamin only, also Li^[10]^ showed that treatment using methylcobalamin and alpha lipoic acid can be more effective when combined with moxibustion therapy. Lan et al^[3]^ study showed that moxibustion can help reduce the Toronto clinical neuropathy score and simple pain scale score (VAS) of DPN patients. Nevertheless, randomize clinical trial done to evaluate the efficacy of moxibustion treatment is still lacking, especially when compared to other treatment like acupuncture therapy.^[11]^

The primary aim of this study is to evaluate the effectiveness and safety of moxibustion therapy on diabetes peripheral neuropathy.

## Methods

2

### Objective

2.1

The main objective of this pilot, interventional, randomized, 2-armed, parallel, singled-masked, controlled trail study is to evaluate the clinical efficacy and safety of moxibustion single treatment in DPN patients.

### Study design and setting

2.2

This study is designed as a pilot, interventional, randomized, 2-armed, parallel, singled-masked, controlled trial. This study will be conducted at TCM Skill Training Centre, Xiamen University Malaysia from November 2021 to December 2023. A total of 40 diabetes mellitus patients with peripheral neuropathy will be recruited to participate in this trial and will be assigned randomly into 2 groups (moxibustion group and waiting group) at 1:1 ratio. The outcome assessor in this study will be unaware of the group assignments. This trial consists of 8-week intervention period and 4-week follow-up period. The study design is illustrated in a flow chart in Figure 1. Present clinical trial study has not completed participant recruitment at the time of submission.

**Figure 1 F1:**
[figure not shown]
Flowchart of the clinical trial.

### Ethics approval and consent to participation

2.3

The protocol was approved by the institutional review board of School of Traditional Chinese Medicine, Xiamen University Malaysia, where the protocol study will take place [Approved ID: TCM/2021/IRB/02]. This clinical trial was registered with the ClinicalTrials.gov Registry No.: NCT04894461 (https://clinicaltrials.gov/ct2/show/NCT04894461?term=NCT04894461&draw=2&rank=1) on May 19, 2021. The clinical trial will be monitored by independent data and safety control. All participants will be providing written informed consent before recruitment.

### Participants

2.4

#### Recruitment

2.4.1

Recruitment will be started on November 1, 2021 (the anticipated date of first enrolment will be November 1, 2021, and the recruitment period may be extended depending on registration during the COVID-19 pandemic status in the Malaysia). A consent document that contains information about the background, purpose, moxibustion intervention, clinical outcome and benefits, and adverse effects will be given to the all participants or their legal surrogates. The investigating clinical researchers will explain the consent details before enrolling the clinical trials and notify all subjects about the option to withdraw without any penalty during the clinical trials.

#### Inclusion criteria

2.4.2

Participants who meet the following criteria will be considered eligible to participate in the clinical study. The inclusion criteria are:

1.Age between 18 and 75 years.2.Diagnosed with diabetes mellitus, according to World Health Organization’ criteria.3.Proven to have peripheral neuropathy.4.Documented consent to participate in this study and acknowledgement that all relevant information is received.5.Willing and able to meet the planned visit and meet the planned schedule, including participation in the experimental investigations.

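### Entry does not require pain although all four primary outcomes are pain assessments, and the Neuropathy Pain Scale is given to patients for whom the article says it is not meant

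*Protocol article*

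**What the plan says.** - **Eligibility (2.4.2, 2.4.3).** Five inclusion criteria cover age, a diabetes diagnosis, neuropathy, consent and availability. The neuropathy item reads "Proven to have peripheral neuropathy". There is no pain requirement, minimum pain score or LANSS cut-off. None of the six exclusions removes patients without pain.
- **Primary outcomes (Abstract, 2.9.1).** The abstract states: "The primary outcome will be pain assessment measured with algometry", followed by LANSS, VAS and NPS. Section 2.9.1 presents each of the four as a pain assessment.
- **Condition on the NPS (2.9.1).** "The NPS is only for use in patients who have already been diagnosed with neuropathic pain".
- **LANSS (2.9.1).** "The possible scores range from 0 to 24, with a score of ≥12 considered to be suggestive of neuropathic pain". The threshold is described but has no role in entry or analysis.
- **Who is measured (2.7).** All four instruments are applied to the participants at visit 1 and again at visits 12, 24 and 25, with no restriction by pain status.
- **The disease (1, 4).** "The main clinical manifestations of DPN includes pain, numbness, paresthesia, and weakness of the lower limbs". The Discussion also speaks of symptoms of this neuropathy that are not painful.

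**The concern.** The entry rule and the primary outcomes describe different populations. A patient with numbness or weakness and no pain satisfies every criterion as written, and is then assessed on four pain measures.

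Two things follow. First, the article sets a condition of use for one of its primary instruments and then schedules that instrument for everyone, with no criterion or procedure that makes the condition true. Following the plan can therefore breach it. Second, on a scale whose lowest value means no pain, a patient who starts there has no room to benefit. Such patients pull the group difference towards zero and pile up scores at the floor. In a trial of 40 this costs precision. It would also blur the effect and SD estimates that a pilot passes on to a later trial.

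**Working it through.** **1. Eligibility against outcomes.** Criteria that concern pain: 0 of 5 inclusion, 0 of 6 exclusion. Primary outcomes that are pain assessments: 4 of 4. Primary outcomes that the article restricts to diagnosed neuropathic pain: 1 of 4, the NPS. The contradiction between 2.4.2, 2.7 and 2.9.1 needs no assumption.

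**2. Which instruments have the floor problem?**

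| Instrument | What the article says | Can a pain-free patient improve? |
|---|---|---|
| NPS | 0 means no pain, 10 the worst | No: stays at 0 or rises |
| Pain VAS | Range not given; lower end taken here as no pain | No, on that reading |
| Algometry | "It is used to determine sensitivity to pain produced by pressure" | Possibly: evoked sensitivity can change without spontaneous pain |
| LANSS | 0 to 24, includes a bedside sensory examination | Possibly: the score need not start at 0 |

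The floor argument therefore covers two of the four measures.

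**3. Size of the dilution, for VAS and NPS only.** The article gives 40 patients at 1:1, so 20 per arm, and a 0.05 threshold, taken here as two-sided. It gives no effect size, SD, power or share of patients with pain, so there is no stated power figure to reproduce. Everything else is assumed:

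- in patients with pain, the mean change differs by 2 points between groups, with SD 2;
- pain-free patients stay at 0 in both arms;
- a share f of each arm has pain.

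Then:

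- difference in means = 2f
- control variance = 4f
- treated variance = 4f + 4f(1 − f)
- mean variance = 4f + 2f(1 − f)
- standardised effect = 2f / √(mean variance)

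For f = 0.7: difference 1.4; variances 2.80 and 3.64, mean 3.22; effect 1.4 / √3.22 = 0.78. Power is from the two-sample t test with 20 per arm.

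| Share with pain f | Difference (points) | Standardised effect | Power, all patients |
|---|---|---|---|
| 1.0 | 2.0 | 1.00 | 87% |
| 0.7 | 1.4 | 0.78 | 67% |
| 0.5 | 1.0 | 0.63 | 50% |
| 0.3 | 0.6 | 0.47 | 31% |

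A second calculation, using a normal approximation, starts from an effect of 0.886 SD, which gives 80% power at 20 per arm. With 25% pain-free, power falls to 56% if the SD is held at 1, and to 64% if pain-free patients have exactly zero change.

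**4. What analysing only patients with pain would recover.** Under the model in step 3, and supposing that pain status is identified perfectly, the subset has 20f per arm and a standardised effect of 1.00.

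| f | Patients per arm in subset | Power, subset | Power, all patients | Gain |
|---|---|---|---|---|
| 0.7 | 14 | 72% | 67% | 5 points |
| 0.5 | 10 | 56% | 50% | about 7 points (56.2 − 49.6) |
| 0.3 | 6 | 35% | 31% | 4 points |

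The gain is small because restriction removes patients as well as dilution. The reason to restrict the NPS analysis is the instrument's stated condition of use; extra power is minor.

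**The case against.** A reader might infer that pain-free patients cannot improve on any primary outcome. The article does not support that. Algometry measures evoked sensitivity and LANSS includes an examination, so both can move in a patient without spontaneous pain. This objection stands and limits the floor argument to the NPS and pain VAS.

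A reader might also infer that a null result could not be told apart from having nothing to treat. That goes too far. Section 2.7 measures all four instruments at visit 1, so a floor at baseline would be visible and could be described. The loss is one of precision, and the result remains interpretable.

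The trial is called a pilot and makes no power claim, and the power figures above rest on assumed inputs. This too stands: they show direction and a plausible range, and say nothing about how many pain-free patients would enrol. It does not dispose of the point, because the article states an efficacy objective and a significance threshold, and the NPS contradiction does not depend on any figure.

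Finally, an obvious repair is to admit or analyse only patients at the article's own LANSS cut-off. The objections to it are sound. The article calls such a score "with a score of ≥12 considered to be suggestive of neuropathic pain", which is weaker than a diagnosis. LANSS is itself a primary outcome, so selecting on a high baseline value invites regression to the mean. This would look like improvement in both arms if the matched-data test in section 3 were used for within-group change. The stated aim also covers diabetic neuropathy in general, so restricting entry changes the question.

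**Conclusion.** The point holds in a limited form. The text alone establishes that patients with non-painful neuropathy are eligible, that every primary outcome is a pain assessment, and that the NPS is scheduled for everyone although the article reserves it for diagnosed neuropathic pain. The eligibility lists are set out as numbered criteria, and the fault lies in what they fix when read against 2.7 and 2.9.1, so this is no detail left to an unseen document.

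The floor effect applies to the NPS and, taking its lower end as no pain, to the pain VAS. Its size is unknown. With a 2-point effect, SD 2, zero change in pain-free patients and 20 per arm, power would fall from 87% to between 67% and 31% as the share with pain falls from 70% to 30%. Confidence is high for the textual mismatch and does not extend to those figures. This should be fixed, but it does not invalidate the trial.

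**What to change.** Reconcile sections 2.4.2, 2.7 and 2.9.1:

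1. Record at visit 1, before allocation is disclosed, whether each patient has diagnosed neuropathic pain, and state how that is established.
2. Analyse the NPS as a between-group comparison in those patients only.
3. Keep all randomised patients in the algometry and LANSS analyses.
4. For the pain VAS, adjust the group comparison for the baseline score, and report the result also in patients with pain at baseline.

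This adds one baseline item and one analysis-set definition, and leaves the population unchanged. The cost is that the NPS analysis will have fewer than 40 patients if any pain-free patients enrol, and will be correspondingly imprecise.

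Alternatively, if the sponsor means to study painful neuropathy only, it may make neuropathic pain an entry criterion and restate the objective to match. That removes the mismatch for all four outcomes, at the cost of a narrower question and slower recruitment. The article says recruitment was not complete at submission, so either change was still possible then.
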